## Abstract

**Background:**

Contrast-induced acute kidney injury (CI-AKI) contributes toward unfavorable clinical outcomes after primary percutaneous coronary intervention (pPCI). We will assess whether hyperuricemia is an independent predictor of CI-AKI and outcomes in patients undergoing pPCI.

**Methods/design:**

Our study is a secondary analysis for the database from ATTEMPT study, enrolling 560 ST-segment elevation myocardial infarction (STEMI) patients undergoing pPCI. Patients will be divided into 2 groups according to the admission serum uric acid (SUA) level. Hyperuricemia will be defined as a SUA level > 7 mg/dL (417 mmol/L) in males and > 6 mg/dL (357 mmol/L) in females. The primary endpoint was CI-AKI, defined as > 25% or 0.5 mg/dL increase in serum creatinine from baseline during the first 48–72 h post-procedurally. Multivariate analyses for CI-AKI and long-term mortality will be performed using the logistic regression and Cox regression analyses, respectively.

**Discussion:**

This study will determine the predictive value of hyperuricemia for the development of CI-AKI and outcomes in patients with STEMI undergoing pPCI. We predict that hyperuricemia will be associated with a risk of CI-AKI in patients with pPCI. Furthermore, after adjusting for other variables, long-term mortality after pPCI may be higher in those with hyperuricemia than in those with normouricemia. Results of this study may provide scientific evidence for the effect of hyperuricemia on CI-AKI and long-term outcomes, thereby offering the potential possibility of lowering SUA on the development of CI-AKI and outcomes.

**Trial registration:**

ClinicalTrials.gov NCT02067195, Registered on 20 February 2014.

## Background

ST-elevation myocardial infarction (STEMI) patients undergoing primary percutaneous coronary intervention (pPCI) are commonly complicated by contrast-induced acute kidney injury (CI-AKI) [1]. CI-AKI is associated with higher hospitalization rates, long-term morbidity, and mortality [2]. Therefore, patients recognized with high-risk factors of CI-AKI should be carefully monitored and treated with appropriate prophylactic strategies. Based on previous study, chronic kidney disease, diabetes, hypotension, contrast volume, congestive heart failure, advanced age, and anemia have been identified as risk factors of CI-AKI [3].

Uric acid is the final product of purine metabolism, which is metabolized by xanthine oxidase [4]. Substantial evidence suggests that hyperuricemia is an independent risk factor for hypertension, metabolic syndrome, chronic kidney disease, and cardiovascular diseases [5]. In previous studies, we reported that hyperuricemia was an independent risk factor for CI-AKI after PCI [6, 7]. However, the conclusion remains controversial [8–15]. In addition, only a limited number of studies reported that hyperuricemia was an independent predictor of CI-AKI in STEMI patients undergoing pPCI. Moreover, it was uncertain about the role of uric acid in the long-term outcome [16–18].

We aimed to investigate the association of hyperuricemia with CI-AKI in patients with high-risk STEMI undergoing pPCI and to determine the predicting role in prognosis.

## Methods/design

### Study design and population

This is a secondary analysis of aggressive hydration in patients with STEMI undergoing pPCI to prevent contrast-induced nephropathy, the first study for reduction of contrast-induced nephropathy following cardiac catheterization (ATTEMPT RESCIND-1 study). Five hundred sixty patients aged 18 years or older, treated with pPCI, and provided written informed consent were included from 15 medical research centers in China. Inclusion and exclusion criteria were described elsewhere [19]. We also excluded the patients without the admission serum uric acid (SUA) level.

### Study protocol

Baseline data will include demographics, diagnosis, medical history, laboratory parameters, medications, and physical examination. Patients will be divided into 2 groups according to the admission serum uric acid (SUA) level. Hyperuricemia will be defined as a SUA level > 7 mg/dL (417 mmol/L) in males and > 6 mg/dL (357 mmol/L) in females. The comorbidities will include hypertension, diabetes mellitus, hyperlipidemia, heart failure, chronic kidney disease, stroke, peripheral arterial disease, and chronic obstructive pulmonary disease. The concomitant therapies were decided by the doctors and were relied on the routine standards of care recommended by the current guidelines. The primary outcome, CI-AKI, was defined as a 25% or 0.5 mg/dL increase in serum creatinine from baseline at 48–72 h after pPCI [19]. The secondary endpoints were different definitions of CI-AKI, persistent renal impairment, major adverse clinical events during hospitalization, total hospitalization costs, and length of hospital stay [19].

Follow-up adverse events will be recorded by trained investigators via office visits or telephone interviews at 3, 6, 12, 18, and 24 months after the pPCI. Long-term outcomes will be major adverse cardiovascular events (MACEs), including mortality, stent restenosis, non-fatal myocardial infarction, and target vessel revascularization.

All data will be collected with standardized electronic case report forms. At the time of enrollment, the data management team of Guangdong Provincial People’s Hospital will conduct consistency checks and issues data clarification forms to deal with discrepant data. All data will be collected after the approval by the ethics committee of all participating centers. An independent data monitoring committee will review the ongoing safety events of every participant.

How data are stored and managed had explained in the “data and safety monitoring board” of our previous study [19]. The details are as follows. A committee of clinicians and a biostatistician, chaired by [name], and [name], MS, who are blinded to the treatment allocation, will periodically review and evaluate the accumulated study data for participant safety, study conduct, and progress, and, when appropriate, efficacy and will make recommendations to the principal investigators concerning the continuation, modification of enrollment, or termination of the trial. Details of any protocol violations (e.g., descriptions, reasons, and resolution) will be reported by the investigators and clinical research associates to the primary investigators, the Central Event Adjudication committee, and Data and Safety Monitoring Board, if necessary. In addition, training will be provided to the researchers, and the study procedure will be supervised, with particular attention to the reasons for bias and data verification to avoid recurrence of protocol violations. Finally, intention-to-treat analysis will be used for the patients with protocol violations instead of the per-protocol analysis [19].

The literature review of hyperuricemia and CI-AKI has reported to the RESCIND group’s academic committee. After that, a statistical scheme will be written and submitted to statisticians and data administrators to obtain data.

### Statistical analysis

Baseline patient characteristics and information will be presented as the mean ± standard deviation or median plus interquartile ranges of descriptive statistics. They will be compared by *t* test or Wilcoxon rank sum test according to distribution. The categorical data about baseline characteristics and information will be expressed as a percentage were analyzed using the Pearson chi-square test or Fisher’s exact test. The association between hyperuricemia and CI-AKI will be performed using multivariate logistic regression analysis. Multivariable logistic regression models have been developed to adjust for clinical characteristics (e.g., age, sex, estimated glomerular filtration rate, left ventricular ejection fraction, chronic heart failure, anemia, diabetes mellitus), and the Mehran risk score will be calculated [3]. All variables that are univariately associated with this outcome measure will be entered as possible predictors in a multivariable logistic regression analysis. The association between hyperuricemia with long-term mortality will be investigated by Cox regression model adjusting for other risk factors (e.g., age, CI-AKI, heart function, renal function, and medication). Kaplan-Meier curve and log-rank test will be performed on the survival time of the hyperuricemia group and the normouricemia group (the cumulative rate of all-cause mortality and MACEs between these two groups). These data will be analyzed on the basis of valid cases. A two-tailed *p* value < 0.05 will be considered statistically significant. The power calculation was based on our previous finding [20], and a CI-AKI incidence of 23% was estimated for the hyperuricemia group, while 11.5% was assumed for the normouricemia group (50% relative reduction). Using a two-sided chi-square test, a significance level of 0.05, and a sample size of 280 each group, the power of the tests is over 90%.

All statistical analyses will be performed using SAS version 9.4 or later (SAS Institute, Cary, NC, USA) and R software (version 3.1.2; R Foundation for Statistical Computing, Vienna, Austria).

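### The primary CI-AKI model has two unreconciled covariate rules, and one of them, univariate screening on the outcome, can omit real confounders and distort the adjusted odds ratio

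*Protocol article*

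**What the plan says.** The aim, in the abstract of the protocol article, is about adjusted association: "We will assess whether hyperuricemia is an independent predictor of CI-AKI and outcomes in patients undergoing pPCI". The Statistical analysis section names the method: "The association between hyperuricemia and CI-AKI will be performed using multivariate logistic regression analysis".

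Two statements about covariates follow in that section.

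- The models are to "adjust for clinical characteristics (e.g., age, sex, estimated glomerular filtration rate, left ventricular ejection fraction, chronic heart failure, anemia, diabetes mellitus", and then "and the Mehran risk score will be calculated". The list is introduced as examples, so it is open. The score is given no role in the model.
- "All variables that are univariately associated with this outcome measure will be entered as possible predictors in a multivariable logistic regression analysis". There is no p-value threshold, no candidate list and no statement that the covariates just named are exempt from the screen.

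The Background section gives the risk factors that the investigators regard as established: "chronic kidney disease, diabetes, hypotension, contrast volume, congestive heart failure, advanced age, and anemia have been identified as risk factors of CI-AKI". Hypotension and contrast volume are in that sentence but not among the example adjusters. The Discussion also ties both to CI-AKI risk in STEMI.

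**The concern.** An independent-predictor claim is only as good as its confounder control. A univariate screen picks variables by marginal significance against the outcome in the data being analysed. A confounder matters when it is related to both uric acid and CI-AKI, and it can matter while failing a significance test, especially with fewer than 100 events. Leaving it out moves part of its effect onto hyperuricemia. The final model is then reported as if its covariates had been fixed in advance.

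The two statements can be read in two ways. If the screen governs everything, then age, eGFR or diabetes can fall out. If the examples are forced in and the screen only adds to them, those are safe, but hypotension and contrast volume are assured of entry only if they pass the screen. The article does not say which reading gives the primary odds ratio, so that choice could be made after the data are seen. The adjusted odds ratio for hyperuricemia, the central number of the study, is at stake.

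**Working it through.** **1. The article's own figure.** Inputs from Statistical analysis: 23% against 11.5%, 280 per group ("Using a two-sided chi-square test, a significance level of 0.05, and a sample size of 280 each group"). Mean rate = (0.23 + 0.115)/2 = 0.1725.
- SE under the null = √(2 × 0.1725 × 0.8275/280) = 0.0319.
- SE under the alternative = √((0.23 × 0.77 + 0.115 × 0.885)/280) = 0.0316.
- Power = Φ((0.115 − 1.96 × 0.0319)/0.0316) = 95.2% (93.9% with continuity correction).

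The stated power of over 90% is reproduced. It belongs to an unadjusted test and is not affected by this point.

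**2. Events available.** 280 × 0.23 + 280 × 0.115 = 96.6. With an assumed split of 140 hyperuricemic and 420 normouricemic: 140 × 0.23 + 420 × 0.115 = 80.5. Excluding patients without admission uric acid would lower both.

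**3. How often a screen misses a real risk factor.** Assumptions: screen at p<0.05, N = 560, overall risk 17.25%, a binary covariate. The miss probability is 1 minus the power of the two-proportion test.

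| Prevalence | OR 1.5 | OR 2.0 |
|---|---|---|
| 20% | 64.5% missed | 23.2% missed |
| 30% | 58.3% missed | 15.8% missed |

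**4. What this does to the hyperuricemia estimate, screen-only reading.** Logistic simulation with N = 560, 17.25% overall risk, half the patients exposed, no true effect of hyperuricemia, seven independent covariates, screen at p<0.05 and 2,000 runs per row. The Monte Carlo SE at 5% is √(0.05 × 0.95/2000) ≈ 0.5 points. The spurious OR is the exponential of the mean log-OR bias.

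| Covariate correlation with the exposure scale | Log-OR for CI-AKI per SD | Mean kept of 7 | Spurious OR, screened | Type I error, screened | Type I error, all 7 forced |
|---|---|---|---|---|---|
| 0.0 | 0.2 | 2.8 | 1.00 | 4.9% | 5.0% |
| 0.1 | 0.1 | 1.0 | 1.07 | 6.0% | 5.6% |
| 0.2 | 0.1 | 1.0 | 1.16 | 9.0% | 5.6% |
| 0.2 | 0.2 | 2.8 | 1.21 | 12.4% | 5.2% |
| 0.2 | 0.3 | 4.8 | 1.14 | 7.4% | 4.6% |
| 0.3 | 0.1 | 1.0 | 1.25 | 14.2% | 4.0% |
| 0.3 | 0.2 | 2.8 | 1.35 | 21.0% | 5.0% |
| 0.3 | 0.3 | 4.9 | 1.27 | 14.0% | 3.9% |

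In the row with 21.0%, loosening the screen to p<0.10 gives 12.0%. With a true OR of 2.3 (correlation 0.2, log-OR 0.2), the 95% interval misses the truth 5.6% of the time when screened and 5.2% with all forced. The log-OR bias is +0.114 against +0.028.

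**5. The other reading, and milder inputs.** Eight confounders, each with CI-AKI OR 1.25 and exposure OR 1.42 per SD, no true effect, 1,500 runs. Each row changes one thing.

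| Setting | Mean OR | Type I error |
|---|---|---|
| All 8 screened at p<0.05 | 1.20 | 11.5% |
| 6 forced, 2 screened | 1.05 | 5.5% |
| 7 forced, 1 screened | 1.02 | 5.3% |
| CI-AKI OR 1.6 per SD | 1.02 | 5.8% |
| Exposure OR 1.15 per SD | 1.09 | 5.7% |
| Mixed directions (5 positive, 3 negative) | 1.04 | 5.2% |
| Screen at p<0.20 | 1.06 | 6.1% |

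The reading of the two statements therefore matters about as much as the confounder strengths do.

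**The case against.** The best defence is that the two statements fit together: the named characteristics are always adjusted for, and anything else that passes the screen is added. Nothing in the text rules this out, and on that reading little harm follows (about 5% to 6% type I error). The article also defers to a statistical scheme still to be written, and its Limitations section concedes that causation cannot be shown.

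Much of this stands. It narrows the point without removing it. The screen is a method that the article states, not a detail left for later. The text does not choose the benign reading, and even that reading leaves two acknowledged risk factors without assured adjustment.

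Several stronger inferences are tempting but are not supported.

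- A reader might see a contradiction with a fixed adjustment list. The list is only illustrative, so the statements are unreconciled, not contradictory.
- A reader might infer that eGFR would be screened out because the endpoint is a relative creatinine rise. The article gives no data on this, and the endpoint also has an absolute 0.5 mg/dL criterion.
- A reader might infer that post-baseline variables will enter, or the Mehran score together with its components. The Study protocol section lists the data concerned as baseline data, and the score is only to be calculated. Because the score and the Background risk factors cite the same reference, overlap is likely, and it is worth excluding in words.

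**Conclusion.** The concern holds in a limited form and should be fixed. The article gives two covariate rules for its primary model without saying which governs, and the screening rule suits an independent-predictor question poorly. It can drop real confounders, bias the adjusted odds ratio, and distort its p-value and confidence interval.

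It would go too far to say that the screen invalidates the inference or that the false-positive rate of this study exceeds 5%. The simulated type I error was about 5% when covariates were unrelated to uric acid or most were forced in. It was 6% to 21% with screening only, and the lowest of these values is barely distinguishable from full adjustment (6.0% against 5.6%). The high values require an assumed p<0.05 threshold and several independent confounders acting in the same direction on uric acid and CI-AKI. The article supplies neither the threshold nor the strengths. The upward direction of the bias rests on the same assumption.

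**What to change.** Delete the univariate-entry sentence. In its place, name one covariate set chosen on subject-matter grounds: the seven listed characteristics plus hypotension and contrast volume. State that all of them stay in the primary model whatever their p-values. State that the Mehran score is used only in a separate model and not beside its own components.

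With hyperuricemia this makes ten parameters if each covariate takes one: 96.6/10 ≈ 9.7 events per parameter with equal groups, or 80.5/10 ≈ 8.1 at the assumed 140/420 split. That is workable.

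The cost is one paragraph of text and a small loss of precision from covariates that prove non-significant. The article reports recruitment as still open and the statistical scheme as not yet written, so the change can be made before the data are obtained.

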## Discussion

CI-AKI is closely associated with prolonged hospital stay, long-term morbidity, and mortality in patient undergoing PCI. The incidence of CI-AKI is about 2% in the general population and over 50% in high-risk population [3]. Previous study supported the relationship between CI-AKI and higher incidence of adverse short- and long-term cardiovascular outcomes, including mortality [21]. Patients with STEMI are likely to present with hypotension, or even cardiogenic shock, higher volume of contrast media, and impossibility of renal prophylactic therapy, which are associated with an increased risk of CI-AKI [22].

Advanced age, diabetes, dehydration, hypotension, sepsis, cardiovascular disease, underlying acute kidney injury, chronic kidney disease, and concomitant use of nephrotoxic drugs were identified as well-known risk factors for CI-AKI [3, 23]. In previous studies [6, 7], we reported that hyperuricemia was an independent risk factor for CI-AKI in PCI patients, which was consistent with other studies [8–13]. However, other studies did not show the same conclusion [14, 15]. Several studies explored the effect of serum uric acid (SUA) on CI-AKI among high-risk patients such as STEMI undergoing primary PCI. Elbasan et al. showed that SUA was associated with CI-AKI in STEMI patients undergoing pPCI (mean SUA = 6.2 ± 0.9 mg/dL, 95% CI, 1.877–3.236; *p* = 0.002) [16]. In another study, Mendi et al. demonstrated that SUA ≥ 5.4 mg/dL was an independent risk factor for CI-AKI (OR 1.26, 95% CI, 1.10–1.42; *p* < 0.001) [17]. Saritemur et al. showed that elevated uric acid was lined with CI-AKI in multivariate analysis after adjusting for potential confounding factors (OR 1.01, 95% CI, 1.00–1.01; *p* = 0.01) [18]. However, even though they reported that high SUA was an independent predictor of CI-AKI in STEMI patients, there was no uniform standard for the definition of hyperuricemia. In our study, we will employ the definition consistent with our previous study.

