### Limitations

Our current secondary analysis is subject to the following restrictions. First, its sensitivity was lower due to the definition of > 0.5 mg/dL because it was less selective for patients with higher risk of mortality and morbidity. Second, single baseline SUA measurements were used to predict CI-AKI and long-term mortality. However, a number of previous studies have used this method as well. Third, the measurement of serum creatinine (SCr) was standardized at 72 h after pPCI rather than at random, which might lead to the ignorance at the increase in delayed SCr (> 72 h). Finally, it is a secondary analysis that is not capable of testifying a causal relationship.

In conclusion, our study will determine the association between hyperuricemia and contrast-induced acute kidney injury (CI-AKI) after primary percutaneous coronary intervention (pPCI) and will identify if hyperuricemia is a risk factor for long-term death after adjusting for CI-AKI.

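### The only covariate-adjusted mortality model conditions on CI-AKI, so no adjusted analysis shows whether admission hyperuricemia itself predicts long-term outcome

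*Protocol article*

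**What the plan says.** **Exposure.** Under Study protocol, "Patients will be divided into 2 groups according to the admission serum uric acid (SUA) level". The exposure is therefore fixed before the procedure.

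**CI-AKI.** The same section says that the primary outcome "was defined as a 25% or 0.5 mg/dL increase in serum creatinine from baseline at 48–72 h after pPCI". Long-term follow-up visits are counted from pPCI and run to 24 months.

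**Mortality model.** Under Statistical analysis, the association of hyperuricemia with long-term mortality is "investigated by Cox regression model adjusting for other risk factors (e.g., age, CI-AKI, heart function, renal function, and medication". CI-AKI stands in that list beside age, with nothing to mark it as a later event.

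**Other long-term analysis.** Kaplan-Meier curves and log-rank tests compare the two uric-acid groups on "the cumulative rate of all-cause mortality and MACEs between these two groups". The Abstract and Statistical analysis name multivariable models for CI-AKI and mortality only. Study protocol names MACE as the long-term outcome.

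**Questions posed.** The Abstract's Background and the main Background ask whether hyperuricemia independently predicts outcomes and what role it has in prognosis. The Abstract's Discussion expects that, after adjustment for variables it does not name, "long-term mortality after pPCI may be higher in those with hyperuricemia than in those with normouricemia". The main Discussion asks whether hyperuricemia still predicts prognosis once CI-AKI is adjusted for, and the conclusion under Limitations says the study "will identify if hyperuricemia is a risk factor for long-term death after adjusting for CI-AKI".

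**The concern.** The article supplies both links of a pathway. For hyperuricemia to CI-AKI, the Abstract states: "We predict that hyperuricemia will be associated with a risk of CI-AKI in patients with pPCI". For CI-AKI to death, the Discussion states: "CI-AKI is closely associated with prolonged hospital stay, long-term morbidity, and mortality in patient undergoing PCI". If both hold, a Cox model with CI-AKI as a covariate estimates only the association that does not pass through CI-AKI.

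That is a different quantity from the prognostic value of a measurement available at admission, because the model needs a result that exists only two to three days later. It also fits poorly with the Abstract's suggestion that the findings may bear on lowering uric acid to improve outcomes, since any benefit acting through CI-AKI is what the model sets aside. The remaining comparison, Kaplan-Meier with log-rank, includes that pathway but leaves two non-randomised groups unadjusted for age, renal function and heart function. The reader of the results would have no estimate that is both adjusted for baseline differences and free of conditioning on CI-AKI.

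**Working it through.** **The plan's own figure.** The only power statement concerns CI-AKI: 23% against 11.5%, 280 per group, two-sided 0.05.
- Pooled rate = (0.23 + 0.115)/2 = 0.1725
- SE under the null = √(2 × 0.1725 × 0.8275/280) = 0.0319
- SE under the alternative = √((0.23 × 0.77 + 0.115 × 0.885)/280) = 0.0316
- z = (0.115 − 1.96 × 0.0319)/0.0316 ≈ 1.66, so power is 95.2% (93.9% with continuity correction)

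This agrees with the stated power of over 90% and is not affected by the present point. The article gives no event count, hazard ratio or power for mortality.

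**Size of the component removed.** Inputs from Statistical analysis are the CI-AKI rates of 23% and 11.5%. The mortality hazard ratio for CI-AKI (H) is not given, so a range is assumed. The ratio of average hazards carried through CI-AKI alone is

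R = [1 + 0.23(H − 1)] / [1 + 0.115(H − 1)]

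The last two columns also assume a direct hazard ratio of 1.5. The share of the log hazard ratio removed is ln R / ln(1.5R).

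| Assumed H | R | HR without CI-AKI in the model (1.5R) | Share of log HR removed |
|---|---|---|---|
| 1.5 | 1.115/1.0575 = 1.05 | 1.58 | 12% |
| 2 | 1.23/1.115 = 1.10 | 1.65 | 19% |
| 3 | 1.46/1.23 = 1.19 | 1.78 | 30% |
| 4 | 1.69/1.345 = 1.26 | 1.88 | 36% |
| 5 | 1.92/1.46 = 1.31 | 1.97 | 40% |

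**Check by simulation** (60,000 subjects, equal groups, two-year follow-up, direct HR 1.5). With H = 2, the hyperuricemia HR was 1.64 without CI-AKI in the model and 1.50 with it. With H = 3, it was 1.83 and 1.56. The ratios of the unrounded estimates, 1.639/1.498 = 1.09 and 1.833/1.564 = 1.17, are close to R.

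**Deaths before the creatinine reading.** The article does not state how these are handled. With H = 3, direct HR 1.5 and an assumed 1% to 3% of patients dying before the reading:
- Coded as having no CI-AKI: the CI-AKI HR fell from 2.9 to between 2.5 and 1.9, and the hyperuricemia HR was 1.51 to 1.59.
- Dropped: the CI-AKI HR stayed at 2.9 to 3.0, and the hyperuricemia HR was 1.44 to 1.49.

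The coefficient at risk is mainly that of CI-AKI.

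**The case against.** The strongest reply is that the adjustment is deliberate. The Discussion and the closing conclusion both pose the question conditionally on CI-AKI, and for that question the model is the intended one. This stands. A reader might infer that the mortality result is simply biased; the document does not support that. The model answers one of two stated questions and leaves the other without an adjusted analysis.

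Several further points stand:

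- An analysis of mortality without CI-AKI is planned, namely Kaplan-Meier with log-rank. It is unadjusted, so it fills the gap only in part.
- A reader might infer that deaths before 48–72 h are mishandled. The article says only that valid cases are analysed. It gives no time origin for the Cox model, no coding of CI-AKI and no landmark, and a condensed article may leave these to the full plan. This is a risk, not a demonstrated error, and in the simulation the hyperuricemia HR moved little.
- A reader might take medication to be another post-procedure covariate. Study protocol lists medications among the baseline data.
- That CI-AKI follows from hyperuricemia is the study's hypothesis. The Background calls the evidence controversial, and Limitations disclaims causal inference.

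It can also be said that an adjusted MACE model is a detail for the analysis plan. But the article does state which outcomes receive multivariable models, and the composite it names as the long-term outcome is not among them.

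**Conclusion.** The point holds in this form: the single covariate-adjusted mortality model conditions on a post-procedure outcome that, on the protocol's own hypotheses, lies between exposure and death. It serves the conditional question in the Discussion and conclusion. It cannot by itself show whether admission hyperuricemia independently predicts long-term outcome, as the Abstract and Background ask, and the Abstract does not say that its adjusted result is conditional on CI-AKI.

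The size is illustrative. The factor of about 1.10 to 1.31 rests on an assumed CI-AKI mortality HR of 2 to 5 and treats the whole difference between 23% and 11.5% as due to hyperuricemia. It is the mediated component only, so conditioning does not erase an association that runs by other routes. The primary endpoint and its power are unaffected.

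**What to change.** 1. Add a Cox model for mortality, timed from pPCI, with hyperuricemia and pre-procedure covariates only. Use it for the question in the Abstract and Background.
2. Fit the same model to time to first MACE, and treat the log-rank comparisons as descriptive.
3. Keep the CI-AKI-adjusted model for the question in the Discussion and conclusion, and label its hazard ratio as conditional on CI-AKI wherever it is reported, including the abstract.
4. State how CI-AKI enters that model. A time-dependent term keeps early deaths in the risk set without classing them as permanent non-cases. A 72 h landmark excludes them openly by design, while the model in step 1 still counts them.

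The cost is a few sentences in the statistical scheme, which the article says is still to be written, and a few extra fits on data already planned for collection. The landmark model loses the early deaths, and with few events its covariate list must stay short.

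### MACE is the named long-term outcome, but the only comparison stated for it is an unadjusted log-rank test between non-randomised uric-acid groups

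*Protocol article*

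**What the plan says.** **Outcome.** The Study protocol section states: "Long-term outcomes will be major adverse cardiovascular events (MACEs), including mortality, stent restenosis, non-fatal myocardial infarction, and target vessel revascularization". Follow-up contacts run to 24 months.

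**Adjusted analyses.** The Statistical analysis section gives CI-AKI a multivariable logistic model. For the long term it states: "The association between hyperuricemia with long-term mortality will be investigated by Cox regression model adjusting for other risk factors". The covariates appear as examples: "adjusting for other risk factors (e.g., age, CI-AKI, heart function, renal function, and medication". The Methods/design part of the abstract draws the same boundary: "Multivariate analyses for CI-AKI and long-term mortality will be performed using the logistic regression and Cox regression analyses, respectively".

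**MACE.** In the Statistical analysis section MACE appears only in the sentence "Kaplan-Meier curve and log-rank test will be performed on the survival time of the hyperuricemia group and the normouricemia group", whose parenthesis covers "the cumulative rate of all-cause mortality and MACEs between these two groups". No covariates or stratification are mentioned. A general two-sided 5% significance rule follows.

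**Exposure.** Patients are grouped by admission uric acid. The Background says: "Substantial evidence suggests that hyperuricemia is an independent risk factor for hypertension, metabolic syndrome, chronic kidney disease, and cardiovascular diseases".

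**The concern.** Mortality receives both a crude and an adjusted comparison. The composite that contains mortality receives only the crude one. The groups are observational, and the article's own Background gives reasons to expect worse renal and cardiovascular status in the hyperuricemia group. For mortality the plan accepts that age, heart function and renal function need adjustment. Nothing in the text explains why the composite would not.

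The abstract's Background sets the aim as independent prediction of CI-AKI and outcomes. The main Discussion asks whether hyperuricemia still predicts poor long-term prognosis once CI-AKI is accounted for. An unadjusted log-rank test answers neither question for MACE. A p value below 0.05 could reflect uric acid, or simply a sicker group.

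**Working it through.** **1. The plan's own figure.** The only design figure concerns CI-AKI: 23% versus 11.5%, 280 per group, two-sided 5%, power over 90%. It reproduces at 95.2% (93.9% with continuity correction). It does not bear on MACE, for which no design figure is given.

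**2. Method by endpoint, as stated.**

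| Endpoint | Crude comparison | Adjusted model |
|---|---|---|
| CI-AKI | not at issue here | logistic |
| All-cause mortality | Kaplan-Meier, log-rank | Cox |
| MACE | Kaplan-Meier, log-rank | none stated |

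The abstract and the Statistical analysis section agree on the last column. The closing paragraph under Limitations also ties adjustment to death.

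**3. Illustration of size. All inputs in this step are assumptions except the 560 patients and the two-sided 5% level.**

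Suppose hyperuricemia has no effect on MACE (true hazard ratio 1). A binary confounder has prevalence p1 in the hyperuricemia group and p0 in the other group, and hazard ratio h for MACE. The crude hazard ratio is then approximately

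HR = [1 + p1(h − 1)] / [1 + p0(h − 1)].

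With D events and a fraction f of patients hyperuricemic, SE(log HR) = 1/√[D f(1 − f)]. The log-rank test rejects with probability P(|Z + log HR/SE| > 1.96). A 24-month MACE rate of 10% to 20% gives D = 56 to 112.

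*One confounder, twice as common in the hyperuricemia group:*
- Mild end: p1 = 0.20, p0 = 0.10, h = 1.5 gives HR = 1.10/1.05 = 1.048. With D = 56 and f = 0.25, SE = 0.309, log HR/SE = 0.15, and rejection is 5.3%.
- Strong end: p1 = 0.50, p0 = 0.25, h = 3 gives HR = 2.00/1.50 = 1.333. With D = 112 and f = 0.50 (the article's 280 per group), SE = 0.189, log HR/SE = 1.52, and rejection is 33.1%.

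*Several independent confounders, each 40% versus 20% with h = 2, f = 0.25 to 0.35, D = 56 to 112:*

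| Confounders | Crude HR | Rejection |
|---|---|---|
| 1 | 1.4/1.2 = 1.17 | 7.9% to 12.2% |
| 2 | 1.167² = 1.36 | 17.0% to 34.3% |
| 3 | 1.167³ = 1.59 | 32.2% to 64.6% |

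With f = 0.50, the one-confounder row becomes 8.9% to 12.9%, so the even split does not reduce the problem. Adjusting for the confounders returns the expected hazard ratio to 1 and the rejection rate to about 5%.

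**The case against.** **A condensed article may leave the model to a later document.** The Study protocol section says a statistical scheme will be written, and nothing shown says MACE will not be modelled. The log-rank sentence also covers mortality, where a Cox model is planned, so it can be read as the usual display beside a regression. This lowers certainty but does not remove the point. The article assigns adjusted models endpoint by endpoint, in the abstract and again in the analysis section, and omits MACE both times.

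**The article makes no explicit claim that MACE will be independently predicted.** This is fair. Its specific adjusted long-term statements concern death, and MACE is neither the primary endpoint nor in the list of secondary endpoints. That limits the weight of the point. The general aim about outcomes and the Discussion's question about prognosis still reach further than mortality.

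**Stronger readings that the documents do not support.**
- A reader might infer that the MACE result will certainly be confounded by renal function, heart failure and age. The Background supports renal and cardiovascular disease as confounders, and heart failure only by implication. Age and heart function appear only as covariates for mortality, which does not show that they differ by uric acid.
- A reader might infer that the article contradicts itself on whether MACE or mortality leads. Mortality is a component of MACE, both are analysed, and neither is ranked. That is an unstated hierarchy, not a contradiction.
- A reader might take the 65% upper rejection rate as a forecast. It needs three factors, each doubled in prevalence and each doubling the hazard. Mild confounding would do almost no harm.

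**Conclusion.** The point holds. As stated, the only comparison for the named long-term outcome is unadjusted, between groups that the article gives reason to think differ in renal and cardiovascular risk. That comparison is likely to be confounded and cannot support a claim of independent prediction of MACE.

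No size can be derived from the documents. Under the assumed single-confounder inputs, the effect ranges from negligible to a false-positive rate of about one in three. Several confounders would push it higher. The primary CI-AKI analysis is unaffected. The change should be made, but it does not undermine the study as a whole.

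**What to change.** In the Statistical analysis section:

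1. Add a Cox model for time to first MACE through 24 months, adjusted for a pre-specified baseline set. A suitable set is age, sex, eGFR, left ventricular ejection fraction or heart failure, diabetes, anemia and randomised hydration arm.
2. Do not simply carry over the mortality model's covariates. That list is given by example, includes unspecified medication, and includes CI-AKI. CI-AKI arises after admission uric acid is measured and may lie on the causal path. Leave it out of the main MACE model, and report a second model that adds it to answer the Discussion's question.
3. Base the MACE conclusion on the adjusted hazard ratio and 95% CI, and label the Kaplan-Meier and log-rank comparisons as descriptive.

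The cost is a few lines of text and one more model, fitted with and without CI-AKI, on data already planned for collection. The adjusted hazard ratio will probably be closer to 1, with a wider interval. The covariate set should stay short: at the assumed 56 to 112 events, the seven covariates above plus hyperuricemia leave 56/8 = 7 to 112/8 = 14 events per term, if each takes one term.
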